**Figure 2**

#### 4.3 Treatment Assignment

- If the participant consents, the research assistant will proceed to randomization via concealed envelopes with
  - Concealed allocation;
  - Stratified on diagnosis:
    - infection,
    - heart failure,
    - chronic obstructive pulmonary disease or asthma, and
    - other diagnosis;
  - Randomly selected block sizes between 4 and 6;
  - Use randomization to determine arm.
- If patient/caregiver does not consent, the research assistant will ask the patient's permission to collect covariates, functional status, and a quality-of-life measure to determine generalizability of enrollment.
- Participants randomized to the control group will receive usual care at the hospital, from an attending general internist.

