574 Documentation by RN/paramedic and MD will occur via digital intake notes, daily progress  
575 notes, and discharge notes that will be compiled (on a secure shared drive) and uploaded as a  
576 scanned document to the patient's chart upon discharge.

[figure not shown]

**Figure 1** RHH flow. Note a patient may **enter** this flow from their home, a clinic, the emergency department, or the hospital floor. The patient is triaged by the RHH nurse with as needed assistance of the RHH MD. The RHH nurse/paramedic deploys in the patient's home, facilitates a medical evaluation by a remote MD, welcomes and educates the patient, and sets up monitoring and communication technology. The nurse rounds at least once daily in person, facilitating an interaction with the RHH MD. Finally, the patient is discharged using the same criteria for discharge as would be used in a traditional hospital (ability to perform activities of daily living given supports in the home).

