#### **5.5 Data to be collected and when the data will be collected**

For both groups we will administer a survey to patients on admission, at discharge, and 30-days post-discharge. For both groups, we will administer a survey to caregivers at admission and 30-days post-discharge.

For the intervention arm only, within 30-days of discharge we will conduct qualitative interviews with the patient and their caregiver (if their caregiver consented to participate in the study, caregiver participation is not required for patient enrollment in this study) (please see more details below).

For the intervention arm, we will ask the rural home hospital MD to complete the MD AM Report each morning and the RHH RN/EMT-P to complete the Nursing visit form after each patient visit. Twice a week we will send the RHH clinicians the Clinician process measures survey. Post-discharge we will conduct qualitative interviews with rural home hospital clinicians only (please see more details below).

For both groups:

Clinical and administrative data will be extracted from electronic sources (e.g., enterprise data warehouse, electronic health record (EHR) at study sites). Cost data for the hospitalization and post-discharge period will be obtained from study site financial personnel using direct cost accounting methods. We will also collect information from patients and caregivers using IRB approved surveys and standardized questionnaires (see below). All data will be collected by trained study staff and inputted on a Partners encrypted shared drive. Data collected from filed research collection (including patient surveys) will be stored in REDCap (Research Electronic Data Capture, Vanderbilt University, Nashville, TN), which is fully HIPAA-compliant secure web application.

- All data collected at Alberta Health Services (Wetaskiwin Hospital) will also be stored on MGB REDCap

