| Duration of 1 st RN visit                                          | RA via RN     | Daily           |
| Duration of subsequent RN visit, in-person                                    | RA via RN     | Daily           |
| Duration of subsequent RN visit, virtual                                      | RA via RN     | Daily           |
| Other metrics captured on the clinician process survey and nursing visit form | RA via RN     | Daily           |
| Insufficient handoff                                                          | RA via RN     | Daily           |
| Documentation error                                                           | RA via RN     | Daily           |
| Equipment malfunction                                                         | RA via RN     | Daily           |

734 **Covariates of Interest**

| Measure                                      | Source                  | Day(s) Obtained |
|----------------------------------------------|-------------------------|-----------------|
| Age                                          | RA via EHR a | Admission       |
| Gender                                       | RA via EHR              | Admission       |
| Race/ethnicity                               | RA via patient          | Admission       |
| Primary language                             | RA via EHR              | Admission       |
| Health insurance status, public/private/none | RA via EHR              | Admission       |
| BMI                                          | RA via EHR              | Admission       |
| Comorbidities, type and #                    | RA via EHR and H&P      | Admission       |
| Partner status                               | RA via patient          | Admission       |
| Education                                    | RA via patient          | Admission       |
| Zip code                                     | RA via EHR              | Admission       |
| Employment                                   | RA via H&P              | Admission       |
| Smoking status                               | RA via H&P              | Admission       |
| Medications used as outpatient, #            | RA via EHR              | Admission       |
| DNR/I code status                            | RA via H&P              | Admission       |
| Lives alone                                  | RA via patient          | Admission       |

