a: Note that RA will recheck covariates after MD H&P completed to ensure comorbidities and other covariates correctly captured

The following data will be collected from intervention arm subjects only (patients, caregivers, and clinicians)

| Measure                                                          | Data sources                                                                                                                         | Day(s) Obtained                                                                                               |
|------------------------------------------------------------------|--------------------------------------------------------------------------------------------------------------------------------------|---------------------------------------------------------------------------------------------------------------|
| RHH admission, daily care, and discharge processes accomplished. | Clinician process measures survey                                                                                                    | Twice a week                                                                                                  |
| Perceived acceptability of RHH care                              | Post-discharge semi-structured interviews with RHH clinicians, RHH patients, and caregivers (separate interview guides are attached) | Patients: within 1 month of discharge

Clinicians: Within 60 days after patient enrollment ends at site |
| Perceived safety, quality of care, caregiver burden              | Post-discharge semi-structured interviews with RHH clinicians, RHH patients, caregivers (separate interview guides are attached)     | Patients: within 1 month of discharge

Clinicians: Within 60 days after patient enrollment ends at site |

Video recordings (intervention group only):

- We will video record some of the telemedicine calls between RHH clinicians and rural home hospitalized patients.

- The video recordings will be for internal quality assurance purposes only.
- The video recordings will not be disseminated in any way (not shared externally)
- We have attached the patient interaction monitoring protocol which provides more detail on this process: “ Site Study Team Protocol- Patient Interaction Monitoring”
- 

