## **6.0 BIOSTATISTICAL ANALYSIS**

### **6.1 Quantitative**

We will present descriptive data with counts and percentages, means and 95% CIs, or medians and interquartile ranges, as appropriate.

The primary outcome (hospitalization cost) will be analyzed between arms, adjusted for site as a fixed effect, which accounts for difference across the three sites. . However, we will present cost data as the percentage of change in mean costs from control (rather than absolute difference) because of the sensitive nature of these data. The primary outcome will be assessed using a generalized linear model assuming a gamma distribution with a log link, given the skewed nature of cost, with treatment arm (control arm as the reference group) and site as fixed effects. The exponential of the treatment effect in this gamma regression model exactly equals the effect of interest (the percentage change from control). Patient characteristics should balance out across the two arms due to randomization, but if not, in the gamma regression, we will adjust for any of the follow patient characteristics that differ across arms: sex, age (continuous), education, and comorbid condition count (continuous). We *a priori* plan to also adjust for COVID case burden at each hospital only if COVID impacted home hospital operations. If the degree of rurality was different between patients at different sites, we *a priori* plan to adjust for degree of rurality.

We will use this same multivariable regression approach for secondary outcomes, using logistic regression for binary outcomes (e.g., readmissions) and negative binomial regression for count outcomes such as days at home, and non-transformed linear regression for normally distributed continuous outcomes (e.g., days at home), as appropriate. Given the multiple comparisons, we will use the Benjamini-Hochberg method for multiple comparisons for the secondary outcomes, with 0.2 as a prespecified false discovery rate.

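### Comorbidity count, a conditional covariate of the primary cost model, may be revised from an H&P completed after allocation, so a recording difference between arms could bias the cost ratio

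*Protocol*

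**What the plan says.** All places are in the protocol.

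- **Order of events (4.3 Treatment Assignment).** "If the participant consents, the research assistant will proceed to randomization via concealed envelopes with" the listed allocation features. No baseline data step is placed between consent and allocation.
- **Source of the count (5.5.3, Covariates of Interest).** The row "Comorbidities, type and" number has the source "RA via EHR and H&P" and the day obtained is admission.
- **Later revision (footnote a to that table).** "Note that RA will recheck covariates after MD H&P completed to ensure comorbidities and other covariates correctly captured".
- **Who evaluates whom.** In the home arm, the Figure 1 legend in section 5.1 has a nurse or paramedic go to the home, who "facilitates a medical evaluation by a remote MD". The same section puts that team's documentation in its own digital intake, progress and discharge notes. For the other arm, section 4.3 says: "Participants randomized to the control group will receive usual care at the hospital, from an attending general internist".
- **Use in the primary analysis (6.1 Quantitative).** The gamma model with log link has arm and site as fixed effects. It is further adjusted for whichever of these differ between arms: "sex, age (continuous), education, and comorbid condition count (continuous". No criterion for a difference is given.

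Nothing in the protocol limits the comorbidity count to information recorded before randomization.

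**The concern.** A baseline covariate is safe to adjust for because allocation cannot have influenced it. Here the count may be completed after allocation is known, from notes that may be written by different clinicians, in different documentation systems, in the two arms. No blinding of the research assistant who does the recheck is described.

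True comorbidity is balanced in expectation by randomization. If one arm's H&P lists more conditions per patient, the recorded counts differ although the patients do not. The rule in section 6.1 would read that as a baseline imbalance, bring the count into the model, and remove from the treatment effect something that was never there. The conditional rule makes matters worse, because the artefact itself switches the adjustment on.

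The direction depends on which arm records more. Over-recording in the hospital arm pushes the adjusted home-to-hospital ratio up and understates a saving. Over-recording in the home arm pushes it down and creates or inflates one. The estimate at stake is the primary one.

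**Working it through.** **The plan's own figure.** The point rests on no stated figure, but the illustration borrows two inputs from the Power analysis: 66 per arm and gamma dispersion 1.2. For a ratio of 0.6, 80% power and two-sided 0.05, the Wald formula gives n per arm = 2 × 1.2 × (1.960 + 0.842)² / (ln 0.6)² = 72.2, so 73 per arm or 146 in total, not 132. Power at 66 per arm is 76.4%. That is a separate matter; 66 is used below only as the planned size.

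**Step 1: can the H&P follow allocation?** Consent leads directly to randomization, and the home-arm evaluation takes place after deployment to the home, hence after allocation. For patients enrolled from home, clinic or emergency department, an H&P completed after allocation is the natural reading, though not a stated one. Early-transfer patients (section 3.3) are already inpatients and may have a hospital H&P beforehand.

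**Step 2: size if recording differs.** Assumptions that are not in the protocol: true count Poisson with mean 4 and balanced; log-cost slope b = 0.10 or 0.15 per condition (roughly 10-15%); a Poisson number of extra conditions with mean d, recorded in the hospital arm only; adjustment when the arm difference has p<0.05; no true cost effect.

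If the count is always adjusted for, the extra noise in one arm attenuates the fitted slope to b × 4/(4 + d/2). The ratio is then multiplied by exp[b × d × 4/(4 + d/2)]. For d = 1 and b = 0.10 this is exp(0.10 × 4/4.5) = exp(0.0889) = 1.093.

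The protocol's rule is conditional, so it was simulated with site in the model, 400 trials per setting. The last column divides the conditional by the unadjusted ratio from the same trials.

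| Extra conditions d | Slope b | Always adjusted (formula) | Adjustment triggered | Unadjusted ratio | Conditional rule | Shift |
|---|---|---|---|---|---|---|
| 0 | 0.10 | 1.000 | 5% | 0.996 | 0.996 | 1.000 |
| 0.5 | 0.10 | 1.048 | 29% | 1.026 | 1.051 | 1.024 |
| 0.5 | 0.15 | 1.073 | 30% | 1.010 | 1.049 | 1.039 |
| 1 | 0.10 | 1.093 | 74% | 0.997 | 1.075 | 1.078 |
| 1 | 0.15 | 1.143 | 76% | 0.997 | 1.106 | 1.109 |

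**Step 3: same settings with a true ratio of 0.60.** The shifts in the same order, leaving out d = 0, are 0.607/0.593 = 1.024, 0.619/0.599 = 1.033, 0.644/0.599 = 1.075 and 0.673/0.599 = 1.124. With one extra condition in the hospital arm, simulated power falls from 0.755 to 0.625 (b = 0.10) and from 0.713 to 0.505 (b = 0.15).

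**Step 4: other direction and another mean.** With a true mean of 3, 1,500 trials per setting and no true effect, extra recording that biases the ratio downward gave conditional ratios of about 0.96-0.98 for half an extra condition. One extra condition gave about 0.92 (b = 0.10) and 0.89-0.90 (b = 0.15).

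**The case against.** **Timing and authorship are inferred.** The tables say only that covariates are obtained at admission. A recheck implies a first capture, which could precede allocation. No section names the author of the H&P, and the count draws on the record as well. Before randomization, in both arms, the home-hospital physician or advanced practice provider reviews the record and decides on admission; clinic and emergency patients have already been assessed. All this is fair, and it is why the point is worded as a possibility. It does not remove the problem: footnote a expressly allows the later revision, and nothing confines the model covariate to the first capture.

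**The size is assumed.** The protocol gives no evidence that either arm records more conditions. With half an extra condition the adjustment is triggered in under a third of trials in the table, and the average shift is small. The standard error of the log cost ratio is about √(2 × 1.2/66) = 0.19, and the design effect is a 40% reduction. This stands as a limit on severity. Unlike sampling error, however, the shift would not average out.

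**The SAP may settle it.** A covariate's definition is often left to the SAP. Here the protocol itself fixes a source and a revision step, so this is not merely missing detail.

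**Stronger readings.** A reader might infer that the baseline questionnaires suffer in the same way, since section 5.5 says: "For both groups we will administer a survey to patients on admission, at discharge, and 30-days post-discharge". The protocol does not support that. Those instruments come from the patient or caregiver, not from an H&P; their order relative to randomization is not stated; and none enters the cost model. A reader might also infer that change from baseline in function or quality of life is compromised, but the protocol states no such analysis. Nor does it support saying that the primary result will be biased.

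**Conclusion.** The point holds as a possible, not demonstrated, bias in the primary cost ratio, confined to the comorbidity count. It rests on text that can be checked: consent followed by randomization, the H&P as a source, revision after it is complete, and conditional entry into the gamma model.

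Under the assumptions above, the shift is about 2-4% for half an extra condition recorded in one arm and about 8-11% for one extra (12% in one setting with a true ratio of 0.60). It can run in either direction and is nil with equal recording. One extra condition would give a spurious effect about as large as the 10% reduction named in the primary aim. Against the 40% reduction used for power, it would distort the estimate more than reverse the conclusion, although it could cost power if the hospital arm records more. It merits a correction because the remedy is cheap.

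**What to change.** Amend footnote a and section 6.1 together. The comorbidity count used in the cost model should come only from records dated before randomization, be extracted by the same rule in both arms, and then be locked. H&P findings made after randomization may be kept as descriptive data, but should not update the model covariate. An H&P that already exists before allocation, as for some early-transfer patients, counts as a pre-randomization record in either arm.

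The rule of adjusting on an observed difference would then respond, for this covariate, only to imbalance that arose by chance.

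The cost is a sentence in each place and an extraction cut-off for the research assistant. The count may be slightly less complete, but equally so in both arms, so precision may suffer a little and no bias between arms is introduced. No clinical procedure changes.

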## 5.5 Standard Operating Procedures for problematic situations

Any subjects presenting with problematic situations will be immediately transferred to the most appropriate hospital and formally withdrawn from the study

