|                                        |                                                              |           |
|----------------------------------------|--------------------------------------------------------------|-----------|
| MRSA                                   | As above.                                                    | Daily     |
| New arrhythmia                         | As above.                                                    | Daily     |
| Hypokalemia                            | As above.                                                    | Daily     |
| Acute kidney injury                    | As above.                                                    | Daily     |
| Medication error                       | As above.                                                    | Daily     |
| Unanticipated mortality                | As above.                                                    | Daily     |
| Loss of consciousness                  | As above.                                                    | Daily     |
| Transfer back to hospital a | RA via MD/RN                                                 | Discharge |
| Unplanned mortality during admission   | RA via MD/RN for home patients; MD EHR review for inpatients | Discharge |
| Unplanned 30-day mortality             | RA via pt/caregiver call                                     | +30       |

a: intervention arm only

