### *Clinically Emergent Patient Condition*

Should a matter be emergent, then 9-1-1 will be called and the patient will be brought to the hospital immediately. An example of an emergent patient condition is severe new-onset shortness of breath.

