### *Clinically Urgent Patient Condition*

Should a matter be urgent, the patient and/or nurse/paramedic and/or physician may choose to communicate via phone or video (either of the 3 persons can initiate either medium). If this is unsuccessful, the nurse/paramedic will attempt to visit the patient in their home. If there is no way to rectify the situation, then the patient will be transported to the hospital. An example of an urgent situation is new-onset non-severe pain.

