### *Unsafe Home Situation*

Should an unsafe home situation be discovered during a home hospital admission, the home hospital team will assess if said situation poses a harm or threat to either the participant or the home hospital personnel. If it does, and after an attempt to rectify said situation, the situation persists, then the home hospital team will end the study and transport the patient to the hospital. An example of an unsafe home situations includes lack of basic sanitation.

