### *Intoxication*

Should intoxication occur in the home of a participant, the home hospital team will assess if said intoxication poses a harm or threat to either the participant or the home hospital personnel. If it does, and after an attempt to rectify said intoxication, the situation persists, then the home hospital team will end the study and transfer the patient to the hospital.

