### *Refusal of care*

Should an enrolled subject refuse standard care at their home despite a clear discussion with the home hospital team, then the subject will be transferred back to the treating hospital and formally withdrawn from the study.

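### The rule that withdraws patients sent from home back to hospital may cost the home arm its outcome data, in that arm only, and conflicts with counting transfer as an outcome

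*Protocol*

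**What the plan says.** The Protocol section Standard Operating Procedures for problematic situations begins: "Any subjects presenting with problematic situations will be immediately transferred to the most appropriate hospital and formally withdrawn from the study". The paragraphs under it differ:

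- **Emergent condition:** "Should a matter be emergent, then 9-1-1 will be called and the patient will be brought to the hospital immediately". Withdrawal is not mentioned.
- **Urgent condition:** phone, video and a home visit come first. "If there is no way to rectify the situation, then the patient will be transported to the hospital". Withdrawal is not mentioned.
- **Unsafe home:** if the threat persists, "then the home hospital team will end the study and transport the patient to the hospital". The paragraph on neglect or child abuse has the same consequence.
- **Intoxication:** "then the home hospital team will end the study and transfer the patient to the hospital".
- **Refusal of care at home:** "then the subject will be transferred back to the treating hospital and formally withdrawn from the study".

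Elsewhere, the Safety table in section 5.5.3 lists "Transfer back to hospital" as a measure, with the footnote "intervention arm only". Section 9.0, Safety monitoring, names the same event for committee review. Section 5.5.1 defines the primary endpoint as total hospitalization cost and gives home hospital accounting as the only source for the intervention arm. Section 5.5.2 takes 30-day readmission and days at home from the EHR and from the patient. The Safety table takes 30-day mortality from a call to the patient or caregiver.

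**The concern.** The rule ties leaving the study to an event that only one arm can have. Control patients are already in hospital. If they deteriorate they stay there and stay in the trial. A home patient who deteriorates to the same degree is moved and, under the opening sentence, withdrawn. Such loss is one-sided and related to outcome, and randomisation does not protect against it.

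At stake are the primary cost comparison and the outcomes that need contact to day 30. An analysis plan that is not shown may well define the population by randomised arm. It could not recover patient reports or telephone follow-up that sites had stopped collecting because the protocol told them the patient was withdrawn.

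**Working it through.** **Side by side.** The opening sentence applies to any subject in a problematic situation, and the first two situations listed are clinical deterioration. Those two paragraphs send the patient to hospital but do not repeat withdrawal, and the urgent one is not immediate. The Safety table and section 9.0 expect transfers to be recorded and reviewed. A site therefore cannot tell from the protocol whether a patient transferred for deterioration is still in the study.

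**Inputs from the protocol.** Primary aim: at least a 10% cost reduction (section 2.1). Power analysis: cost ratio 0.6, gamma dispersion 1.2, 66 per arm, two-sided 0.05, 80% power. No transfer or withdrawal rate and no relative cost is given.

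**Assumptions.** A share *f* of home patients is transferred, 5–15%. Their mean cost is *m* times that of other home patients, 1–3.

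**Effect on the cost ratio.** With the other home patients' mean set to 1, the full home-arm mean is (1 − f) + f·m. If transferred patients are dropped, the observed mean is 1. The ratio is understated by 1 − 1/((1 − f) + f·m):

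| f | m = 1 | m = 1.5 | m = 2 | m = 3 |
|---|---|---|---|---|
| 5% | 0% | 2.4% | 4.8% | 9.1% |
| 10% | 0% | 4.8% | 9.1% | 16.7% |
| 15% | 0% | 7.0% | 13.0% | 23.1% |

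For example, f = 10% and m = 2 gives 1 − 1/(0.90 + 0.20) = 1 − 1/1.10 = 9.1%. A true ratio of 1.00 is then seen as 0.91, a true 0.90 as 0.82 and a true 0.60 as 0.55.

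**Effect on the test.** I simulated 20,000 trials per setting with no true saving, 66 randomised per arm, dispersion 1.2, and a Wald test on the log ratio without site terms. The table shows how often the result was significant in favour of home (nominal 2.5%) when transferred patients were dropped:

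| f, m | Favouring home |
|---|---|
| 5%, 2 | 4.9% |
| 10%, 2 | 7.9% |
| 10%, 3 | 16.3% |
| 15%, 3 | 27.7% |

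With every patient and all cost kept, the rate was 2.8–3.9%. With m = 1, dropping patients left it at about 3%.

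**Loss of numbers.** This matters less. The plan's own figure does not reproduce exactly: 2 × 1.2 × ((1.960 + 0.842)/ln 0.6)² = 72.2, so 73 per arm, and 66 per arm gives 76.4% power. That is a separate matter and nothing here depends on it. Losing 5–20% of the 66 home patients lowers 76.4% to 75.3–71.4%.

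**The case against.** A reader might infer that the sickest and costliest home patients are certain to be excluded, and that every outcome is therefore biased towards home hospital. The documents do not support that.

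- No passage says that withdrawn patients' data are discarded. Analysis populations are commonly left to the statistical analysis plan.
- The emergent and urgent paragraphs, which concern the patients most likely to be costly, do not repeat withdrawal. The explicit wording sits with unsafe home, intoxication, neglect and refusal, where higher cost is not shown.
- Transfers are to be recorded and reviewed, and section 5.5 takes clinical, administrative and cost data for both arms from electronic and finance sources. Part of the data could survive withdrawal.
- The transfer rate and cost multiple are assumed. With a multiple of 1 there is no cost bias. At the design ratio of 0.6, exclusion exaggerates a real saving and does not create one.

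All four points stand, and they limit the claim to what may happen. They do not remove it. The opening sentence is unqualified and covers deterioration, its trigger exists in one arm, and some 30-day outcomes rest on contact with the patient or caregiver. The protocol nowhere says that such contact continues after withdrawal.

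**Conclusion.** The point holds as a conflict in the protocol that opens the way to one-sided loss of follow-up. It does not show that patients will be excluded. If the rule is followed literally and transferred patients cost more, which is plausible for emergent and urgent transfers, the primary cost ratio favours home. Under the assumed ranges the understatement is 0% to 23%. At 10% transferred and twice the cost it is 9%, so a home arm with no saving would nearly show the 10% reduction in the primary aim. Bias in readmission, days at home, 30-day cost and mortality is likely but not certain, and its direction is not established for transfers without deterioration. Because the primary endpoint is exposed and the wording can be amended, this should be corrected in the protocol and not left to the analysis plan.

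**What to change.** Leave the transfer rules as they are. Reconcile the problematic-situations section with the Safety table and section 9.0 by separating two events:

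- **End of home hospital care.** Where the text now says withdrawn, or that the study ends, state that home hospital care ends and the patient remains in the study. The patient is analysed in the arm randomised and followed to day 30.
- **Leaving the study.** Only the patient's withdrawal of consent ends data collection.

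Amend the source entry in section 5.5.1 so that the home arm's index cost includes the receiving hospital's cost after transfer. Without this, retained patients could still be under-costed.

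The cost is mainly a wording amendment. Obtaining cost data takes some extra effort when the receiving hospital is not a study site, which the rule allows. The home-arm estimate may be less favourable than under exclusion.
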